#### 12.4. Final Analysis

When the trial has been completed, a point estimate and a 95% confidence interval will be computed for  $p$  using the method of Jovic and Whitehead, which allows for the sequential nature of the trial. If the trial has to be abandoned before the stopping rule is met due to lack of patients, or for any other reason that is independent of the emerging results of the trial, then an underrunning analysis will be used to compute a point estimate and a 95% confidence interval for  $p$ . This will also allow for the futility stopping rule imposed (Whitehead, 1992).

#### 12.5. Inclusion in Analysis

It is important to note that the primary sequential analysis described uses only data from patients who were admitted more than 14 days previously. Although it may be known that some more recently recruited patients have already died, their data will not yet be used, to avoid bias due to information on death being available sooner than information on survival. Enrolled patients who die within 48 hours of admission to the ETU will be excluded from the analysis.

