## 12. STATISTICS

## 12.1. Description of Statistical Methods

The trial is designed to determine whether TKM is a promising treatment for Ebola. No early stopping in the case of evidence of efficacy is proposed, as there are currently only 100 courses of TKM available so early general roll out of the treatment is not possible. Enrolling the full 100 patients will maximize the precision of the final estimate of efficacy.

A futility design (Whitehead and Matsushita, 2003) is therefore used to allow early stopping in the event of evidence of futility or harm. This approach will recruit up to 100 patients, but will stop if the number of successes observed so far falls below a certain threshold.

In order to avoid early stopping due to enrollment of patients with very severe, late Ebola virus disease, who may not be expected to be salvaged even by an effective antiviral therapy, the stopping rule will be calculated after exclusion of enrolled patients who die within 48 hours of admission to the ETU.

For the purposes of determining futility, the effectiveness of the treatment will be judged in terms of the probability that a patient allocated to TKM treatment will survive to D14, after excluding patients who die within 48 hours of admission to the ETU. This probability will be denoted by  $p$ . Note that  $p$  represents the true value of the probability rather than any estimate that might be found from the trial data. The value  $p = 0.55$  will be used for guidance. If  $p \leq 0.55$ , then the treatment will be regarded as 'not promising' and the trial will be terminated.

The choice of guide value for  $p$  has been made following an analysis of individual level data on patients from a Ebola Treatment Centres from this current outbreak at Gueckedou, Foya, Kailahun and Elwa 3. Data on the outcomes of 1592 patients with laboratory confirmed Ebolavirus infection from these four centres are shown in Table 3. Only data from adults have been included, and data on patients who died on the day of admission or on the following day, or else the day after that have been omitted.

**Table 3:** Estimates and 95% confidence intervals for the probability of surviving to Day 14 following admission to the treatment centre, excluding patients who die on the date of admission or on the day after or the day after that. Success is taken to be a difference between the date of death and the date of admission that is  $> 13$  days.

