## 12.2. The Number of Participants

The maximum number of participants available to evaluate the drug efficacy is 100. The data will be analysed sequentially and stopping rules applied.

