### 12.3. Criteria for the Termination of the Trial

Research sites will inform the data management centre every time that a patient is allocated to TKM treatment. Fourteen days after admission, they will report to the data management centre whether that patient did, or did not, survive to D14. Every time that a D14 report is received on a patient, a point will be plotted on Figure 5. This is plot of the number of survivals (S) reported so far against the number of D14 reports received (n), after excluding from both S and n those patients allocated to TKM treatment who died within 48 hours of admission. The plot is compared with the lower red boundary shown. If the plot reaches this boundary, the trial will be stopped with the conclusion that treatment with TKM is not promising. This safety plot will ensure a rapid reaction if TKM proves to be ineffective or harmful in the short term.

If the plot continues above the boundary until the green boundary is reached, corresponding to D14 reports being received from 100 patients, then it will be concluded that TKM is a promising treatment. If the trial has to be terminated before 100 patients have received TKM and before the lower red boundary is reached, and if stopping is due to a shortage of eligible patients rather than to any safety concerns, the final dataset will be analysed. If the outcomes of patients recruited are good enough it remains possible for TKM to be found promising, even following an incomplete study. Nevertheless, every effort will be made to complete the study of 100 patients if the lower boundary is not crossed and no important safety concerns emerge.

**Figure 5.** The stopping rule for the trial

[figure not shown]

The properties of the design have been calculated exactly, based on the independent Bernoulli distributions of each patient outcome. These are shown in Table 4 and depict the specified probability of reaching the most appropriate conclusion for a range of values of  $p$ . It can be seen that the probability is declaring TKM to be promising is set at 0.025 according to this design. Recommending a treatment associated with such a low probability of survival to D14 would be considered a type I error, and the risk

of this has been set at the conventional value of 0.025. The power of correctly identifying TKM as promising when  $p = 0.70$  is 0.827.

**Table 4:** Probabilities of claiming that TKM is promising for the phase II trial of Treatment TKM

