#### 12.7. Rationale for statistical design choice

In the context of the current EVD outbreak, a simple, robust and rapid trial is essential. Mortality dominates all other patient endpoints. Most deaths occur within 14 days of diagnosis, and so survival (or

not) to D14 represents the most relevant clinical endpoint. The situation at Ebola Treatment Centres is highly challenging, and so this study places minimal additional responsibilities on them.

A design with a lower stopping boundary is proposed so that, if the trial is to conclude that TKM is not promising, this can be done as quickly as possible. If all treated patients die before D14, then only 8 patients will be required. No early stopping in the case of evidence of efficacy is proposed, as there are currently only 100 courses of TKM available so that no early general roll out of the treatment is possible. Rapid reporting of minimal information would appear to be feasible, and in keeping with the urgency of the situation. Until the trial is terminated, data managers need only compare the number of survivals observed so far with the stopping boundary **Error! Reference source not found.** A table of values will be provided for this purpose.

The approach described is a form of the futility design, as described by Whitehead and Matsushita The analysis is based on an orderings approach introduced by Fairbanks and Madsen. Exact calculations have been made for this particular design, using SAS, and this package will be used for the analysis.

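### Sections 12.3 and 12.5 hold known deaths out of the stopping plot until Day 14 with no exception for a crossing that is already certain, so allocation can continue after the conclusion is fixed

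*Supplement*

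**What the plan says.** All references are to protocol v2.9.

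- **When an outcome counts.** Under Section 12.3, sites report each patient's status 14 days after admission, and the plot sets survivals (S) against Day 14 reports received (n). Deaths within 48 hours of admission leave both counts. Section 12.6 allows entry to slip to Day 16.
- **Early deaths.** Section 12.5 restricts the sequential analysis to patients admitted more than 14 days earlier: "Although it may be known that some more recently recruited patients have already died, their data will not yet be used". The reason given is that deaths become known before survivals.
- **Action.** "If the plot reaches this boundary, the trial will be stopped with the conclusion that treatment with TKM is not promising" (12.3).
- **Stated benefits.** "This safety plot will ensure a rapid reaction if TKM proves to be ineffective or harmful in the short term" (12.3). "If all treated patients die before D14, then only 8 patients will be required" (12.7).
- **After stopping.** Section 12.4 gives an estimate for a completed trial and an underrunning analysis for one abandoned early. It does not mention patients whose outcomes are pending when the boundary is reached.

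**The concern.** A death cannot be reversed. Once enough early patients have died, no outcome among those still pending can keep the plot off the boundary. The plan nevertheless waits for the Day 14 reports. Apart from the staggered first four patients in Section 7.4, no rule in the protocol pauses allocation meanwhile.

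The reason in Section 12.5 supports keeping early deaths out of the plot as ordinary data, since that would overstate mortality. It does not apply to a check that gives every pending patient the best possible outcome. Such a check can only bring forward a stop that is bound to occur.

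At stake are patients allocated to a drug whose verdict is already fixed, and part of a supply of 100 courses.

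**Working it through.** **1. Inputs from the plan.** "The value $p = 0.55$ will be used for guidance" (12.1). At that value "the probability is declaring TKM to be promising is set at 0.025 according to this design" (12.3). "The power of correctly identifying TKM as promising when $p = 0.70$ is 0.827" (12.3). "The maximum number of participants available to evaluate the drug efficacy is 100" (12.2). The earliest stop is 8 reports with no survivor (12.7).

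**2. Reproducing the design.** Figure 5 is not shown, so the boundary is reconstructed: stop if S ≤ floor(0.682n − 4.854). At n = 7 the bracket is −0.08, so no stop is possible. At n = 8 it is 0.602, so S = 0 stops. An exact Bernoulli recursion to n = 100 gives the probability of claiming that TKM is promising:

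| p | 0.50 | 0.55 | 0.60 | 0.65 | 0.70 | 0.75 | 0.80 |
|---|---|---|---|---|---|---|---|
| Table 4 | 0.002 | 0.025 | 0.158 | 0.487 | 0.827 | 0.973 | 0.998 |
| Reconstructed | 0.0017 | 0.0249 | 0.1584 | 0.4866 | 0.8272 | 0.9725 | 0.9979 |

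The largest gap is 0.0005, so the reconstruction serves for what follows.

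**3. A crossing can be certain early.** At n = 12 the bracket is 0.682 × 12 − 4.854 = 3.33, so S ≤ 3 stops. If 9 of the first 12 patients are known to have died and 3 are pending, S cannot exceed 3. The crossing is fixed, yet the plan waits.

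**4. Why the check is exact.** Take the distance above the line, S − (0.682n − 4.854). A survivor adds 1 − 0.682 = 0.318, a death subtracts 0.682, and a patient later excluded as a 48-hour death adds 0. Survivor is therefore the best case for any pending patient, exclusions included. If the line is reached on that assumption, the plan's own plot must reach it too, provided patients are taken in admission order. The same trials stop, so Table 4 stands.

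**5. Allocations at stopping if all die.** Assumptions: first four patients staggered, then a steady rate r per day; allocation one day after admission; reports at 14 days; deaths spread evenly over days 3 to 8 or days 3 to 13. The eighth report comes 13 days after the eighth allocation, so about 8 + 13r patients are allocated by then. At r = 1 that is 21, or 20 if a patient allocated on the day of the report is not counted. The curtailed figures are simulated.

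| Rate per day | Plan as written | With best-case check | Difference |
|---|---|---|---|
| 0.05 | 8 | 8 | 0 |
| 0.1 | 9 | 8 | about 1 |
| 1/3 | 12 | 9–10 | 2–3 |
| 1 | 20–21 | 12–15 | 5–8 |
| 2 | 33–34 | 17–23 | 11–17 |

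With Day 16 entry the plan's figure rises to about 22 at 1 per day and 37 at 2 per day.

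**6. Not only when all die.** At true survival 0.40 and 1 per day, about 30 are allocated under the plan against 22 to 25 with the check. At 0.55 and 1 per day, among trials that stop, about 48 against 40 to 44. In 7,200 simulated trials at survival 0 and 0.40, half of them with 10% early exclusions, no decision differed.

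**The case against.** - **The rule is deliberate and simple.** Section 12.5 gives a reason, and Section 12.7 wants little extra work for sites and a single comparison for data managers. The reason holds for the plot but does not reach a best-case check. The point on workload stands in part: Section 12.3 asks for outcomes only at Day 14, so curtailment needs a prompt death report that the plan does not now require.
- **There are other safeguards.** The IDMC reviews the first four patients (7.4), sees safety data again after 15 are treated (7.3), receives SUSARs at once (11.2) and works to a charter not shown here (14). It could act sooner, and nothing obliges it to let allocation run on. But no stated rule ties its action to known deaths.
- **The size is not in the documents.** Correct. Section 7.2 says only that daily numbers will be capped. Much of the excess is also ordinary outcome delay: at 1 per day the check still leaves 12 to 15 allocated.

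Three stronger readings are tempting, and the documents do not support them.

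- A reader might infer that the 8 in Section 12.7 is wrong. The rule counts Day 14 reports, and in that unit 8 is exact.
- A reader might infer that pending patients at stopping are inevitable. Below about one patient per 13 days there would be none, although at that pace the other 92 would take 92 × 13 = 1,196 days, over three years.
- A reader might infer that pending patients are dropped, against Section 7.5. Section 12.5 governs when data enter the sequential analysis, and secondary outcome 1a in Section 6 counts Day 14 mortality in everyone allocated. Section 12.4 is silent on their place in the estimate of p, which is a gap and not a contradiction.

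**Conclusion.** The point holds as a worthwhile, inexpensive improvement. It is not an error in the test: type I error, power and every entry of Table 4 stand. Followed as written, Sections 12.3, 12.5 and 12.6 let allocation continue after the verdict of not promising has become certain. At 1 allocation per day and total mortality, roughly 5 to 8 of about 12 allocations made after the eighth would fall in that period. The number shrinks to nothing at very slow accrual and grows with faster accrual.

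That no decision changes follows from the linear form of the boundary and from taking patients in admission order. The patient numbers rest on the reconstructed boundary and on assumed accrual, death timing and a one-day gap to allocation. They should be read as ranges, not forecasts.

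**What to change.** 1. **Sections 12.3 and 12.5.** Keep the Day 14 rule for the plot itself. Add: at each reported death and each Day 14 report, list allocated patients in admission order, leave out known 48-hour deaths, score every pending patient as a survivor, and stop if the boundary is reached even so. State that Day 14 outcomes are also plotted in admission order, because Section 12.3 now plots them as reports arrive.
2. **Section 12.3, reporting.** Ask sites to notify the data management centre promptly of any death in a patient allocated to TKM.
3. **Section 12.7.** Say that 8 means eight Day 14 reports in patients who survived the first 48 hours, and that more patients may have been allocated by then. This is a point of wording.
4. **Section 12.4.** Add an overrunning analysis for patients already allocated with outcomes pending when the boundary is reached, next to the underrunning analysis.

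The cost is one extra report per death, a look-up table for the data managers and a few sentences of text. Sample size, boundary and error rates do not change.

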#### 12.6. Procedure for Accounting for Missing, Unused, and Spurious Data.

While considerable effort will be made to ensure all patients are followed up at D14, D30, month 3, 6 and 12 (through return visits to clinic, phone, email or field-researcher visits), some patients may not be contactable. Leeway will have to be allowed for late reporting, but this should be limited: it may be that data on survival to D14 is not entered until Day 16 in order to avoid remaining bias due to late reporting of survival. However, if it turns out that a patient died on Day 15 or later, *then they are survivors* for the purpose of this study. If they walked away on Day 7, seemingly cured, it might be assumed that they survived to Day 14. Some judgment will necessarily be used here.

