| Trial Design                       | Open-label, single arm trial, with a concurrent observational study                                                                                                                                                                                                                                                                                                                                                                              |                                                                                                                                                                                                                                                                                                                                                                                                                                                                                                                                                                                                                                                                                                      |
| Trial Participants                 | Patients with confirmed Ebolavirus disease attending the participating treatment centre                                                                                                                                                                                                                                                                                                                                                          |                                                                                                                                                                                                                                                                                                                                                                                                                                                                                                                                                                                                                                                                                                      |

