## **9. DATA COLLECTION**

### **9.1. Clinical data acquisition**

Study dosing, sampling and data collection will begin after enrolment. Figure 3 shows the clinical data acquisition schedule.

Patient demographic data and medical history will be collected for all patients at the time of enrolment in the trial. While a participant is an inpatient, information will be collected daily on signs and symptoms, medications and blood products received, and the results of non-trial blood samples. For patients who are receiving TKM that day, detailed records of physiological monitoring and adverse event monitoring (outlined in section 8.2) will be provided.

SD1 (Study Day 1) is defined as the first day these data are collected. For patients who are in the TKM cohort this is likely to be the same day the first dose is administered.

These data will be collected daily for participating patients up to D14, or discharge, or death, whichever occurs first. Patients who achieve discharge criteria before D14 will stop the inpatient testing schedule upon discharge.

For patients not enrolled in the study, only anonymous survival data will be collected.

Discharge criteria are:

- 72 hours without fever or significant symptoms AND
- A significant improvement in clinical condition AND
- Able to feed, wash and walk independently AND
- Ebolavirus RNA PCR test negative

Figure 3: Clinical data acquisition procedures

[figure not shown]

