|             | Gueckedou | Foya  | Kailahun | Elwa 3 | Overall |
|-------------|-----------|-------|----------|--------|---------|
| Lower limit | 0.485     | 0.428 | 0.514    | 0.510  | 0.517   |
| Estimate    | 0.535     | 0.495 | 0.568    | 0.554  | 0.543   |
| Upper limit | 0.585     | 0.562 | 0.622    | 0.598  | 0.569   |

As a result of this analysis,  $p = 0.55$  has been set as the success rate threshold above which TKM would be considered promising.

While children are initially excluded from the TKM arm of the trial, if the eligibility criteria is expanded to age  $>5$  following IDMC review of preliminary results, TKM trial data from adults and children will be jointly analysed, since the availability of TKM is restricted to 100 treatment courses and a stratified analysis is infeasible. Case fatality is highest in children aged  $< 5$  years, after which it declines with age reaching a minimum in persons aged about 15-20 years. Therefore the inclusion of subjects aged 5-17 years is not expected to inflate the case fatality, and the futility threshold of  $p \leq 0.55$  is expected to remain valid.

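### Section 12.6 lets an untraced patient be scored a D14 survivor by unspecified judgement, with no criterion, named scorer or sensitivity analysis; the error this causes depends on how many of them died

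*Supplement*

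**What the plan says.** The synopsis describes the design as "Open-label, single arm trial, with a concurrent observational study". Under section 12.3, sites report to the data management centre whether each patient allocated to TKM was alive at D14. Each report adds a point to a plot of survivors (S) against reports received (n), and touching the lower boundary stops the trial. If 100 reports arrive without touching it, TKM is declared promising. Section 12.1 says that p = 0.55 "has been set as the success rate threshold above which TKM would be considered promising". On the type I error, section 12.3 says that the risk "of this has been set at the conventional value of 0.025".

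Section 12.6 accepts that some patients may not be reachable. Its only rule for scoring them concerns a patient who left on Day 7 looking recovered: "it might be assumed that they survived to Day 14. Some judgment will necessarily be used here". It does not say who judges, on what evidence, by when, or whether with knowledge of the plot. It says nothing about patients who leave while still ill. Section 8.9 records outcome after withdrawal only where this can be done. Sections 12.4 to 12.6 contain no best-case or worst-case analysis.

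Section 9.1 already defines four discharge criteria that must all be met, beginning with "72 hours without fever or significant symptoms AND" and ending with a negative Ebolavirus PCR. Section 12.6 does not refer to them.

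**The concern.** Survival to D14 is the primary endpoint, the sole input to the stopping rule and the basis of the final estimate. Scoring an unknown as a survivor is harmless when the patient lived. When the patient died, it moves S up by one that should not be there. With one arm compared against a fixed 0.55, no control group carries the same misclassification to offset it, and open-label conduct means that an impression of recovery is formed with the treatment known.

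Section 12.5 guards against the pessimistic bias: it withholds recent patients because deaths become known sooner than survivals. Section 12.6 leaves the optimistic direction to discretion. At stake is the nominal 0.025 risk of calling an ineffective drug promising.

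**Working it through.** **Inputs from the protocol.** Maximum n = 100 (12.2). Null value p = 0.55 (12.1). Type I error 0.025 and power 0.827 at p = 0.70 (12.3, Table 4). One anchor for the boundary (12.7): "If all treated patients die before D14, then only 8 patients will be required".

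**Step 1: reproduce Table 4.** Figure 5 is not shown, so straight lower boundaries that first stop an all-death path at n = 8 were searched. The best fit stops when S ≤ b(n) = floor[0.6825 × (n − 7.167)]. This gives b(7) = −1, b(8) = 0 and b(100) = 63, so at least 64 survivors are needed at n = 100. The exact recursion is f(n, s) = p·f(n−1, s−1) + (1−p)·f(n−1, s), with f(n, s) set to 0 for s ≤ b(n). P(promising) is the sum of f(100, s) over s.

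| p | Table 4 | Recomputed |
|---|---|---|
| 0.50 | 0.002 | 0.0017 |
| 0.55 | 0.025 | 0.0249 |
| 0.60 | 0.158 | 0.1588 |
| 0.65 | 0.487 | 0.4876 |
| 0.70 | 0.827 | 0.8282 |
| 0.75 | 0.973 | 0.973 |
| 0.80 | 0.998 | 0.998 |

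Neighbouring lines agree to about 0.003 over p = 0.55 to 0.62.

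**Step 2: effect of misclassification.** Let u be the share of patients scored as survivors without data and q the true death risk among them. The success probability that the plot sees at a true 0.55 is p_rep = 0.55 + u·q. The protocol gives neither u nor q, so both are assumptions shown as ranges.

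*All of them died (q = 1):*

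| True deaths scored as survivors, per 100 | p_rep | P(promising) | Multiple of 0.0249 |
|---|---|---|---|
| 1 | 0.56 | 0.039 | 1.5 |
| 2 | 0.57 | 0.057 | 2.3 |
| 3 | 0.58 | 0.083 | 3.3 |
| 5 | 0.60 | 0.159 | 6.4 |

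The last row needs no reconstruction: Table 4 itself gives 0.158 at p = 0.60, and 0.158 / 0.025 = 6.3.

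*Only some of them died:*

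| Unknowns per 100 | q | p_rep | P(promising) |
|---|---|---|---|
| 3 | 0.10 | 0.553 | 0.029 |
| 3 | 0.45 | 0.5635 | 0.044 |
| 5 | 0.05 | 0.5525 | 0.028 |
| 5 | 0.10 | 0.555 | 0.031 |
| 5 | 0.45 | 0.5725 | 0.063 |

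Here q = 0.45 is the null death risk, 1 − 0.55.

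**Step 3: the opposite error.** Scoring true survivors as deaths at p = 0.70 gives p_rep = 0.70 − v, where v is the share so scored. Power falls from 0.828 to 0.774 (v = 0.01), 0.711 (0.02), 0.640 (0.03) and 0.488 (0.05; Table 4 gives 0.487 at p = 0.65).

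**The case against.** Section 12.6 describes someone who walked out apparently recovered a week after admission, and such a patient probably did survive. Section 8.3 provides phones, D14 and D30 visits, phone follow-up and possible outreach, and lets primary outcome data be collected later, so unknowns may be few and many would be resolved. This stands, and it limits the size of the problem. It does not say how to score the patients who remain, or those who left while ill.

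Four stronger readings are tempting, and the documents do not support them.

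- *A few untraced patients are enough to multiply the type I error.* Only if they died. Five unknowns per 100 at a 5-10% death risk give about 0.03. A correct call of survival introduces no bias.
- *The staff who judge can see how close the plot is to the boundary.* Nothing says so. Sites report to the data management centre (12.3), and data managers make the comparison (12.7). The supportable point is that no scorer is named and no separation is specified.
- *The benchmark was free of such judgement.* Table 3 classifies success from the dates of death and admission. It does not say how untraced discharged patients were counted, so no asymmetry with 0.55 is shown.
- *Untraced patients should be fixed as deaths by Day 16.* That would clash with the later collection allowed in section 8.3. Section 12.6 mentions Day 16 only as a possible delay in entry. Step 3 shows that the cost in power could be heavy.

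The discharge criteria are also not wholly objective, since one asks for significant clinical improvement. They are, however, prespecified and include a PCR result.

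**Conclusion.** The gap is real: the primary endpoint can be filled in by unspecified judgement, in the favourable direction, in a design with no control arm to absorb the error and no sensitivity analysis to expose it. Its size is conditional. For 1 to 5 true deaths per 100 scored as survivors, the type I error rises from 0.025 to between about 0.04 and 0.16. For five unknowns per 100 it ranges from about 0.03 at a low death risk to about 0.06 at the null risk. These figures assume independent outcomes, constant misclassification over the trial and a reconstructed boundary that matches Table 4 closely. The share of unknowns and their death risk cannot be taken from the documents. The change is worth making because it is cheap and removes discretion, not because serious inflation has been shown to be likely.

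**What to change.** Replace the last two sentences of section 12.6 with a prespecified rule:

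- An untraced patient recorded as meeting all four section 9.1 discharge criteria before leaving counts as a D14 survivor.
- Any other untraced patient is not scored a survivor by judgement. The patient is held as unknown while tracing continues, and is updated if later contact under section 8.3 establishes D14 status.
- The rule is applied from the case report form by someone without sight of the boundary plot. As the data management centre receives the reports and its data managers make the boundary comparison, this needs a stated separation of tasks.
- The boundary comparison and the final estimate are reported twice, with all remaining unknowns counted as deaths (worst case) and as survivors (best case). The plan should state in advance which comparison governs stopping if the two disagree.

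The cost is a few sentences and a little more analysis. The worst case is conservative: at p = 0.70, 1 to 2 true survivors per 100 counted as deaths lower power from 0.83 to about 0.77-0.71, and five lower it to about 0.49. For that reason it is proposed as a reported bound beside the best case, not as a permanent scoring of untraced patients.
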